## Abstract

**Background:**

Condom use can reduce the risk of infection by human papillomavirus (HPV). Furthermore, it has been suggested that condom use can increase the regression rate of cervical lesions. In Denmark, women with cervical intraepithelial neoplasia grade 2 (CIN2) and a future wish to conceive are not treated immediately but are followed up by a gynecologist about 6 months later. The aim of this project was to determine if advising women to have their male partners to use a condom during sexual intercourse in the follow-up period can increase the regression rate of CIN2.

**Methods/design:**

This is a randomized clinical trial of women with CIN2. The intervention group was advised to use condoms between the date of diagnosis and the date of their follow-up visit. The control group received standard care. Cervical samples were tested for HPV. The primary endpoint will be the intention-to-treat analysis with the relative rate of CIN2 regression between the intervention group and the control group. Regression is defined as <CIN2 at the follow-up visit. In addition, a per-protocol analysis of the regression rate in women adhering to condom use compared with the control group will be performed. The secondary endpoint will be the HPV-clearance rate in the condom group.

**Discussion:**

If condom use for 6 months can enhance the regression of cervical lesions, then more women can be spared conization. This is an efficient treatment of cervical lesions but is associated with an increased risk of preterm delivery.

**Trial registration:**

ClinicalTrials.gov, NCT02907333. Registered on 14 September 2016.

**Electronic supplementary material:**

The online version of this article (10.1186/s13063-019-3564-4) contains supplementary material, which is available to authorized users.

## Background

In Denmark, women aged 23–49 years are invited to a cervical screening every 3 years and women aged 50–64 years every 5 years [1]. Liquid-based cytology samples are collected by their general practitioner [2], and women with severe abnormalities are referred directly to a gynecologist. Every year, almost 400,000 cytology samples are taken, of which 40,000 are abnormal [3], resulting in 25,000 biopsies and 6,000 conizations [4]. Control of cervical cancer via screening, therefore, implies that many women attend repeated control visits or undergo conization. In Denmark, conization is performed using the loop electrosurgical excision procedure [5].

An examination by a gynecologist includes a colposcopy, a biopsy, and collecting a cytology sample. If her histology is normal or she has cervical intraepithelial neoplasia grade 1 (CIN1), the woman will, according to national guidelines [6], be followed up by her general practitioner, who will collect a new cytology sample after 6–12 months. If the woman is diagnosed with CIN2 and has a wish to conceive in the future, the recommendation is a follow-up visit to a gynecologist for a biopsy after 6 months. Women with CIN2 and with no wish to conceive or postmenopausal women are recommended to undergo conization. Women with CIN3 are always recommended to undergo conization [6].

Persistent infection with high-risk (HR) human papillomavirus (HPV) is a necessary but not sufficient condition for cervical cancer [7]. HPV is the most common sexually transmitted infection. Almost 75% of sexually active women become infected at some point in their life [8]. Most women will clear the infection, but for some women the infection persists, and for a very small number of women, the infection progresses to cervical cancer [9].

Male condom use (or, simply, condom use) has been shown to confer considerable protection against HPV infection, though the protection is less perfect than for other sexually transmitted diseases [10, 11]. Furthermore, condom use has been hypothesized to improve the regression rate of cervical lesions [12]. Firstly, condom use may reduce HPV infection and reinfection, and thereby allow the immune system to repair a cervical lesion. Secondly, semen has an immunosuppressive effect, which is considered an advantage in the reproductive process, but when cervical lesions have developed, the absence of semen could benefit the cellular immune response [13–15]. Lastly, the latex used for condoms is a foreign material that could enhance the cellular immune response and contribute to regression of a cervical lesion.

Two small studies found an increased regression rate of cervical lesions when condoms were used in the short term [16, 17], but this finding was not supported by a small questionnaire-based study [18]. The studies were too small to provide conclusive evidence, and condom use cannot, therefore, be included in the current guidelines for the management of CIN.

### Objective

The purpose of the present randomized controlled trial was to provide further evidence for the effect of condom use on the regression of cervical lesions. The hypothesis was that the regression rate would increase if condoms were used consistently for 6 months between the time of diagnosis and the follow-up visit to a gynecologist.

## Methods/design

### Patient and public involvement

Focus group interviews were performed prior to the project start with women in the relevant age groups. They advised on the design of the project, the intervention, and the duration of the intervention. Study participants were not involved in the recruitment or the conduct of the study.

### Study design

This was a randomized controlled clinical trial embedded in the routine diagnostic and follow-up visits to gynecologists for cervical lesions. It was a non-blinded study with a parallel allocation to an intervention group and a control group. The randomization ensured that there were two comparable groups of women, all following standard care according to national guidelines [6]. The intervention group were advised to use condoms to increase the regression rate of cervical lesions. The control group were not given this advice. Figure 1 is the SPIRIT diagram for the project.

**Fig. 1 Fig1:**
[figure not shown]
SPIRIT diagram of the project stages. CIN2 Cervical intraepithelial neoplasia grade 2

### Target population

Inclusion criteria:Premenopausal women with histologically confirmed CIN2Aged 18 to 45 yearsA 6-month follow-up examination with a gynecologist has been scheduled

Exclusion criteria:Women with a latex allergyWomen who are pregnantWomen already in a follow-up program for a cervical lesion

#### Intervention group

Women in the intervention group are called by the project physician and informed about the project. They are advised always to use condoms during intercourse until the next follow-up visit with a gynecologist. If they have not been reached after two calls, a text message is sent. If they have not been reached after a further two calls and one text message, they are considered missing. Those contacted either consent or do not consent to participate verbally. Participant information and the informed consent form is sent to the home address of women who consent. Free condoms are sent to the woman once the signed informed consent form has been returned to the project physician. As a reminder about adherence, a text message is sent halfway through the intervention period. Participating women continue with their previous contraceptives if any. At the end of the intervention period, a questionnaire is sent by email. The questionnaire requests information on use of contraceptives, age at first intercourse, lifetime number of sexual partners, frequency of sexual intercourse, condom use in the intervention period, number of sexual partners in the intervention period, smoking, number and time of births and abortions, and HPV vaccination. The intention was to send the questionnaire to all women in the intervention group at the time of follow-up. However, the ethics committee of the Capital Region has stipulated that the questionnaire is sent only to women who have consented to condom use.

For women in the intervention group, their diagnosis at the follow-up visit with a gynecologist is retrieved from the pathology register [19]. For participating women, samples from both baseline and follow-up visits to a gynecologist are tested for HPV.

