#### Control group

Women in the control group are not contacted by the project physician and therefore, not given advice on condom use as a way to enhance regression of their cervical lesions. Otherwise, they are examined and treated in exactly the same way as women in the intervention group. The biopsy result from the follow-up visit at the gynecologist is retrieved from the pathology register.

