#### Secondary endpoint

The secondary endpoint is clearance of HR-HPV for women who consented to condom use, based on the baseline sample and the follow-up sample. Clearance is defined as having a HR-HPV type at the time of CIN2 diagnosis that is not present at the follow-up. Previous studies have showed that having HPV16 will decrease the chance of regression of a CIN lesion [20]. Therefore, the initial HPV status and phenotypes might influence the regression rate of cervical lesions.

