### Data analysis plan

The relative regression rate (RRR) for CIN2 in the intention-to-treat analysis will be calculated as$$ \mathrm{RRR}=\frac{\left(\mathrm{number}<\mathrm{CIN}2\ \mathrm{at}\ \mathrm{follow}\hbox{-} \mathrm{up}\ \mathrm{in}\ \mathrm{in}\mathrm{tervention}\ \mathrm{group}\right)/\left(\mathrm{all}\ \mathrm{women}\ \mathrm{in}\ \mathrm{in}\mathrm{tervention}\ \mathrm{group}\right)}{\left(\mathrm{number}<\mathrm{CIN}2\ \mathrm{at}\ \mathrm{follow}\hbox{-} \mathrm{up}\ \mathrm{in}\ \mathrm{control}\ \mathrm{group}\right)/\left(\mathrm{all}\ \mathrm{women}\ \mathrm{in}\ \mathrm{control}\ \mathrm{group}\right)}. $$

The relative HPV-clearance rate (RCR) is calculated as$$ {\displaystyle \begin{array}{l}\mathrm{RCR}=\\ {}\frac{\left(1-\mathrm{number}\ \mathrm{HR}\hbox{-} \mathrm{HPV}+\mathrm{at}\ \mathrm{follow}\hbox{-} \mathrm{up}\ \mathrm{in}\ \mathrm{in}\mathrm{tervention}\ \mathrm{group}\right)/\left(\mathrm{number}\ \mathrm{HR}\hbox{-} \mathrm{HPV}+\mathrm{at}\ \mathrm{baseline}\ \mathrm{in}\ \mathrm{in}\mathrm{tervention}\ \mathrm{group}\right)}{\left(1-\mathrm{number}\ \mathrm{HR}\hbox{-} \mathrm{HPV}+\mathrm{at}\ \mathrm{follow}\hbox{-} \mathrm{up}\ \mathrm{in}\ \mathrm{control}\ \mathrm{group}\right)/\left(\mathrm{number}\ \mathrm{HR}\hbox{-} \mathrm{HPV}+\mathrm{at}\ \mathrm{baseline}\ \mathrm{in}\ \mathrm{control}\ \mathrm{group}\right)}.\end{array}} $$

These calculations are possible because we have a closed population, in which all women recruited are followed up for the entire observation period. Logistic regression will be used to analyze the questionnaire data as predictors of outcomes. SAS version 9.4 will be used for the analysis.

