### Data sources

From the gynecologists, we will receive the name, date of birth, and phone number of women who have consented to be contacted. Every second week, we will receive a list from the pathology register [19] with new CIN2 diagnoses. Sample results from the follow-up visits as well as HPV status at baseline and follow-up will be retrieved from the pathology register. Data on adherence to condom use will be obtained from the questionnaires. All data will be linked via the women’s unique personal identification number. The Danish Data Inspective Agency has approved the handling and storage of data (SUND-2016-21). All study-related material will be stored safely. Personal information on the participants is stored in secure computer systems.

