### Strengths and limitations

A strength of this study is its design as a public health randomized controlled trial embedded in the routine treatment and follow-up program for women with cervical lesions. This gives us two groups of women who are comparable except for the intervention. It is, furthermore, a strength to have three regions included. In Denmark, health care is paid for by the government and is free of charge [26], but there are minor regional variations in clinical procedures, and recruiting participants from three regions ensures that there is a representative sample of women.

The number of drop-outs is a limitation in this project. We do not receive consent to be contacted from all women attending a gynecologist, some women in the intervention group cannot be reached by phone or text message, and some women do not want to participate. Participating women may, therefore, be a selected group. Furthermore, adherence to condom use is inevitably self-reported. This information is collected from questionnaires at the end of the project, so there could be some recall bias. A punch biopsy may alter the HPV infection, and the disappearance of a type-specific HPV infection can be caused either by a biopsy or by an actual clearance. As the study is embedded in the clinical setting, we are not able to validate histology diagnoses or perform p16 staining. However, as the routine diagnostic procedures are used for both the intervention group and the control group, any possible misclassification will affect the two groups equally.

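### HR-HPV clearance is defined as a one-arm endpoint in consenting women but analysed as a ratio to a control rate whose data source is not stated

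*Protocol article*

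**What the plan says.** **Endpoint.** The abstract states: "The secondary endpoint will be the HPV-clearance rate in the condom group". The Secondary endpoint section agrees: "The secondary endpoint is clearance of HR-HPV for women who consented to condom use, based on the baseline sample and the follow-up sample". Neither names a comparator. That section counts clearance as the loss of a high-risk type that was present at diagnosis.

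**Data by arm.** Under Intervention group, the follow-up diagnosis is retrieved for the whole arm, but HPV testing is stated for a narrower set: "For participating women, samples from both baseline and follow-up visits to a gynecologist are tested for HPV". In that section, participation means having agreed when called by the project physician. Under Control group, women are not contacted, and the result named is histology: "The biopsy result from the follow-up visit at the gynecologist is retrieved from the pathology register".

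**Data without an arm.** Data sources adds: "Sample results from the follow-up visits as well as HPV status at baseline and follow-up will be retrieved from the pathology register". The abstract's statement that cervical samples were tested, and the statement under Setting that pathology departments agreed to send samples, also name no arm.

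**Analysis.** The Data analysis plan introduces a ratio with "The relative HPV-clearance rate (RCR) is calculated as". It needs four counts: HR-HPV positives at baseline and at follow-up, in the intervention group and in the control group.

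**The concern.** The endpoint and testing sections describe one arm, while the analysis section needs two. The numerator does not match either: the formula refers to the intervention group, whereas the endpoint and the stated testing cover only the consenting part of it.

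This is the only named secondary endpoint, and an RCR reads as the effect of the condom advice on HPV clearance. If control results are missing, the ratio cannot be formed and only a one-arm rate remains. If consenters are set against all controls, the ratio can be formed but randomisation no longer protects it. The article itself concedes that participating women may be a selected group.

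**Working it through.** **The plan's own figure.** No rate, effect size or power is given for HPV clearance. The only sample size, 140 per group, is for CIN2 regression. It reproduces: 0.6 × 0.55 + 0.4 × 0.22 = 0.418 against 0.22, two-sided 0.05 (assumed), 95% power and pooled variance give 142 per group. The sample size is not at issue here.

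**The four inputs of the RCR against the stated data collection**

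| Count needed | Stated source |
|---|---|
| Intervention, HR-HPV+ at baseline | Testing stated for consenting women only |
| Intervention, HR-HPV+ at follow-up | Testing stated for consenting women only |
| Control, HR-HPV+ at baseline | None by arm; the Data sources sentence might cover it |
| Control, HR-HPV+ at follow-up | None by arm; the same sentence might cover it |

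**Why one arm is not enough.** Clearance in consenters mixes natural clearance, the effect of the biopsy and any condom effect. Background says most women clear HPV. Strengths and limitations says that "the disappearance of a type-specific HPV infection can be caused either by a biopsy or by an actual clearance". Only a concurrent comparator measured in the same way separates these.

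Illustration with assumed rates: let clearance in consenters be 40% and control clearance be x, so RCR = 0.40 / x.

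- x = 20%: 0.40 / 0.20 = 2.0
- x = 30%: 0.40 / 0.30 = 1.33
- x = 40%: 0.40 / 0.40 = 1.0
- x = 50%: 0.40 / 0.50 = 0.8

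The same one-arm result fits a doubling, no effect or a reduction.

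**Why consenters against all controls is not enough.** For regression, the Primary endpoint section plans to use the rate in women who declined as a check on selection. The same check for HPV would need results in women who declined, and testing of those women is not stated.

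**The formula as printed.** Each term reads (1 − number positive at follow-up) / (number positive at baseline), which subtracts a count from 1. Take assumed counts of 84 consenters (60% of 140, equating expected condom use with consent) and 140 controls, all positive at baseline, with 42 and 105 still positive:

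- As printed: (1 − 42)/84 = −0.488 and (1 − 105)/140 = −0.743; ratio 0.66.
- Evidently intended: (1 − 42/84)/(1 − 105/140) = 0.50/0.25 = 2.0.

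The printed version nearly equals the ratio of persistence, (42/84)/(105/140) = 0.67, so its direction is reversed.

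**Two definitions of clearance.** A woman who loses her baseline type but carries another high-risk type at follow-up has cleared under Secondary endpoint. Under the formula, which counts any HR-HPV positivity, she has not.

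**The case against.** The strongest reply is that a reader might infer that controls are untested, and the article does not say so. The testing sentence sits under Intervention group and describes what happens there. The Control group section names the biopsy result without calling it the only one, and says of controls: "Otherwise, they are examined and treated in exactly the same way as women in the intervention group". Three statements on HPV testing or retrieval name no arm, and the register could hold control results. The article condenses a fuller protocol, and its two SPIRIT figures are not available here. This stands: missing control data is a possibility, not an established fact. But the sentence on equal treatment concerns examination and care, and the sections that do specify by arm point towards one-arm testing.

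A reader might also infer that the secondary endpoint cannot be computed. That goes too far. Clearance in consenting women can be computed from the stated testing; only the RCR is in doubt.

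A third tempting inference is that control results would come from a different assay or a selected subset. Nothing in the article describes this, so it is a matter to ask about.

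Finally, the biopsy problem is disclosed, and the intended guideline recommendation rests on CIN2 regression. That limits the consequences, but it does not reconcile the endpoint with its analysis.

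**Conclusion.** The inconsistency is on the page: the endpoint is described in one arm and analysed as a ratio of two, with a numerator population that differs from the endpoint population. As written, the article does not show that the RCR can be formed. If it were formed as consenters against all controls, it would not be a randomised comparison. A one-arm rate does not estimate a condom effect.

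The size is not identified, because the documents give no clearance rate in either arm. The RCR range of 2.0 to 0.8 and the reversal from 2.0 to 0.66 rest wholly on assumed figures and show the mechanism only. The misplaced 1 in the formula and the two definitions of clearance need no assumption.

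This should be fixed, but it does not threaten the trial. The intention-to-treat analysis of regression, its sample size and the register histology in both arms are untouched.

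**What to change.** Reconcile the abstract, Intervention group, Control group, Secondary endpoint, Data analysis plan and Data sources. First state whether HPV status at both visits exists for controls and for intervention women who declined, and from what source.

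- **If it is available from the same source in both arms:** define the RCR over all randomised women HR-HPV positive at baseline, by allocated arm. Report the fraction with results per arm, and treat the analysis of consenters as supportive.
- **If it is not:** delete the RCR. Report clearance in consenting women as a descriptive proportion with a 95% CI, and state that it does not estimate a condom effect.
- **In either case:** choose one definition of clearance, either loss of a baseline type or absence of any HR-HPV, and use it throughout. If the formula is kept, write each term as 1 − (number positive at follow-up / number positive at baseline), with both counts taken in women positive at baseline.

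The cost is wording, with no new testing. A causal claim about HPV clearance may have to be given up.

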#### Control group

Women in the control group are not contacted by the project physician and therefore, not given advice on condom use as a way to enhance regression of their cervical lesions. Otherwise, they are examined and treated in exactly the same way as women in the intervention group. The biopsy result from the follow-up visit at the gynecologist is retrieved from the pathology register.

### Setting

The project takes place in three out of the five regions of Denmark. The project started in September and October 2016 in the Central Denmark Region and Region Zealand at both public hospitals and with gynecologists in private practice. The two regions were chosen because data from the pathology register showed that 700 study subjects would be expected per year, and the regions had relatively few stakeholders. To speed up recruitment, the project was expanded in the fall of 2017 to include some private practice gynecologists from the Capital Region.

In the Central Denmark Region, all hospitals and all gynecologists in private practice agreed to participate, but recruitment was not possible from two gynecologists in private practice due to logistical challenges. In Region Zealand, all hospitals and nine gynecologists in private practice agreed to participate. However, three gynecologists in private practice did not participate. It was not possible to recruit patients from one private practice due to their use of non-standard treatment. The Capital Region has four gynecology departments and 50 gynecologists in private practice. We asked 12 gynecologists in private practice to participate in the project, and five accepted (Table 1). The project physician has visited all gynecologists to provide standardized information.

**Table 1 Tab1:** Number of gynecologists contributing to the project by region

Region in Denmark	Gynecologists in private practice		Hospital gynecology departments	
	Yes	No	Yes	No
Central Denmark Region	7	2	4	0
Capital Region	5	7	Not contacted	
Region Zealand	8	4	4	0

The gynecologists in hospitals and private practice send samples to the regional pathology departments for analysis. In Region Zealand and in the Capital Region, one pathology department per region is responsible for the analysis, while the responsibility is shared between departments in the Central Denmark Region. All pathology departments have agreed to send samples for HPV analysis.

All women included in the study are treated according to national guidelines. Women referred to a gynecologist after an abnormal cytology result undergo a colposcopy-guided biopsy. Samples are taken from sites with visible cellular changes and also from random sites. It is recommended that four or five samples are collected during each biopsy examination. The transformation zone in the cervical canal should be assessed with a cytobrush or by endocervical curettage. This procedure is recommended at the time of diagnosis and at the follow-up visit [6].

